## Abstract

**Objective:**

To describe the protocol of the MOVI-ageing randomized controlled trial, a home-based eHealth intervention of cognitive-demanding exercise for older adults, in improving global cognitive function and basic cognitive functions, cardiorespiratory fitness, and muscle fitness.

**Methods:**

This randomized controlled trial will include participants identified in the social centers of Cuenca and Talavera de la Reina who agree to participate and provide informed consent. Adults aged 60–80 years of both genders retired regardless of the reason for retirement, who do not meet frailty criteria according to Fried criteria, and without cognitive impairment will be invited to participate. This study will be developed in two phases: (i) a 12-week randomized efficacy/feasibility trial and (ii) a large-scale implementation randomized trial phase with a 12-week follow-up following similar procedures. In addition, a qualitative study on barriers to and facilitators of the implementation of the physical exercise intervention using eHealth for older people will be conducted. Participants will have access to a platform including videos of cognitively demanding physical exercise. The participants will be remotely and off-line guided through the physical exercise intervention, and the research team will be able to check the degree of compliance with the program and its correct execution. The participants will receive feedback on their compliance with the routines and reinforcement messages.

**Implications:**

The implementations of the findings and their inclusion in guidelines may directly impact in older people’s life, and relatives, through the prevention of morbidity and the reduction of years lost to disability. These benefits may be reflected in the reduction of economic expenditure by reducing the demand for social and health care services.

**Ethics:**

The Clinical Research Ethics Committee of the ‘Virgen de la Luz’ Hospital in Cuenca approved the study protocol (registration number: 2022/PI3222). In addition, this protocol was previously registered in Clinicaltrials.gov (Number: NCT05928078).

## Introduction

Although there is significant heterogeneity in the aging process, it is accompanied by a general decline in functional capacity, mainly related to the process of sarcopenia and to oxidative and inflammatory processes associated with arterial aging (1, 2). Age-related physiological and pathological changes and the complications arising from them have a major impact on lifestyle (1). Good muscle capacity is essential for the maintenance of functional ability and the promotion of quality of life (QoL). Aging-related declines in strength and respiratory capacity are well-known causes of decreased walking speed and increased mobility limitations and disabilities among older individuals, all of which are risk factors for institutionalization and mortality (3). In addition, declining health is associated with functional limitations, restricted social interaction, and impaired mental health status, including reduced cognitive function, neurodegeneration, and the development of dementia (1).

Moreover, cognitive impairment is one of the most common causes of disability in developed countries among the older adults (4). Cognitive decline and dementia place social and economic pressure on the governments of nations, which is expected to increase as a new case of dementia is diagnosed every 4 s (5–7). This means that approximately 115 million older people worldwide are likely to suffer from Alzheimer’s disease/dementia by 2050. Although the economic costs are enormous, the combined economic and social burden of dementia is even more daunting, as it corresponds to the burden of people with dementia and their families and is, therefore, difficult to calculate (8). In view of this situation, the World Health Organization (WHO) emphasizes the importance of taking comprehensive actions against cognitive impairment and dementia and urges governments and institutions to develop prevention strategies that reduce the risk of cognitive decline (6, 9).

Without ignoring the importance of nutritional and lifestyle modification interventions, physical exercise is the primary therapeutic strategy for the prevention of disease and associated decline in functional capacity (10). Evidence suggests that enriching physical exercise interventions with a cognitive challenge could maximize the neuroplastic properties of physical exercise. The additive effects of cognitively demanding physical exercise could be explained by the temporal nature of peripheral brain-derived neurotrophic factor (BDNF), which returns to basal levels 10–60 min after physical exercise, requiring a temporal succession of cognitive demands to optimally benefit from these neurotrophic effects (11). Furthermore, the brain plasticity favored by increasing cell proliferation and synaptic plasticity is “guided” by cognitive training by increasing the number of new-born neurons that survive and their integration in new neural networks, as well as the increased number of synapses in preexisting neural networks (12). It has been suggested that these effects could be observed regardless of age, and therefore cognitive decline could be preventable (13).

## Aims

The purpose of this paper is to describe the protocol of the MOVI-ageing randomized controlled trial, a home-based eHealth intervention of cognitive-demanding exercise for older adults, in improving global cognitive function and basic cognitive functions, cardiorespiratory fitness, and muscle fitness.

## Methods

### Design

For the design of this protocol, the CONSORT guidelines for randomized controlled trials studies (14) and the Consolidated Criteria for Reporting Qualitative Studies (COREQ) (15) were used. The MOVI-ageing randomized controlled trial will include a mixed design, following quantitative and qualitative approaches.

The quantitative study will be developed in two phases: (i) an efficacy and feasibility study and (ii) an implementation study. The former will be aimed at testing the efficacy of the MOVI-ageing intervention in improving key outcome variables, refining the intervention, and examining potential biases of the intervention. During this phase, a qualitative approach will be used as feedback to define the development of the platform, as evidence indicates that when users are involved in the design and evaluation of the feasibility study, the efficacy of the implementation increases. The latest will be developed following the same methodological procedures to test the MOVI-ageing intervention in a larger sample size.

### Recruitment and allocation

The Clinical Research Ethics Committee of the ‘Virgen de la Luz’ Hospital in Cuenca has approved the study protocol (registration number: 2022/PI3222). The development of this project will be supported by the Health Care Services of Cuenca. In addition, this protocol has been previously registered in Clinicaltrials.gov (Number: NCT05928078).

Potential participants will be accessed through key informants in the social centers of Cuenca and Talavera de la Reina. The research team will contact the potential participants by phone to offer them participation in the study. In addition, flyers and posters will be located in places where older people could potentially develop leisure activities (including but not limited to libraries and older adults’ centers) with the contact information of the research team.

During the information process of the participants, the research team will inform them that they can drop out of the study as they request. After agreement to participate and informed consent, participants will be randomly distributed (1:1) to the intervention (IG) or control group (CG) using EPIDAT 4.2 software (Figure 1).

**Figure 1 fig1:**
[figure not shown]
Flow chart of trial participants. CG, control group; IG, intervention group.

Although the application of a physical intervention program cannot be blinded to participants, the investigators involved in measurements will be blinded to the group to which the participants belong. With the same aim, each participant will receive an identification number to blind his/her allocation during the analysis of data. The identification number and the personal data of the participants will be stored in different data bases and will be crossed only in case to detect anormal values during the measurement processes.

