### MOVI-ageing intervention: description

The MOVI-ageing intervention will be developed as a randomized controlled trial with two arms in which participants will be randomly assigned to the IG, in which a home-based e-Health intervention of cognitively demanding exercise will be performed, or to the CG in which participants will continue their regular daily activity.

The e-Health intervention will be delivered using a platform including videos that will guide the participants in the realization of the movement during the cognitively demanding physical exercises. The participants will follow the videos remotely and off-line, and the users will have to imitate the movements of the trainer. Through the platform, it will be possible to evaluate the degree of compliance with the exercise program and the correct performance, as the system will accurately track and measure the participant’s limb movement through the camera and provide the research team with an objective measure of the patient’s movements and progress. Research team will be able to check this information during the development of the session or at any time of the clinical trial duration.

The recorded videos, designed by a team of experts including nurses, psychologists, physical activity graduates, and geriatricians, will include cognitively demanding exercises involving both basic cognitive functions (i.e., inhibition, working memory, and cognitive flexibility) and higher cognitive functions (i.e., spatial orientation, numerical calculation, and semantics). Each video will include a standardized physical exercise program structured as follows: 5 min warm-up (including animation and/or joint mobility activities), three blocks of 4 min at 65–75% of the maximum heart rate (including aerobic and muscle strength activities) without cognitive demand, three blocks of 4 min at moderate intensity including cognitively demanding activities, and 10 min of cool-down (including balance activities, breathing-relaxation exercises, and/or muscle stretching) (Figure 2).

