#### Criteria for nonadherence and prolongation of training

Compliance with the exercise program will be regularly monitored through the intervention. To be considered in the analyses, participants must attend at least 70% of the sessions. If, due to unexpected circumstances, a participant does not comply with the exercise program within the 12 weeks, the training program may be extended for up to 4 weeks. Finally, in case of unexpected adverse effects of the intervention, the participant will be clinically followed-up, and the research team will record the reasons for drop out.

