#### Analyses of outcomes

After measurements, participants’ data will be entered into a database by two independent researchers. Blinding on handling data will be assured by separating measurement values from general participant information.

The statistical analysis plan can be summarized as follows: (i) after checking that randomization has been effective, we will winsorize the variables to limit the influence of extreme values; this will be done by replacing values below the 1st percentile with the 1st percentile value and those above the 99th percentile with the 99th percentile value. (ii) Mixed regression models will be used in which each outcome variable will be the dependent variable, interventions will be treated as fixed effects (1 = IG and 0 = CG), and the models will be adjusted for baseline reference values and age. The results will be expressed as absolute differences in changes in the variables between baseline and final measurement. When the dependent variable is dichotomous, odds ratios (ORs) will be calculated. Finally, (iii) analyses will be conducted from an intention-to-treat perspective, whereby participants will remain in the group to which they were originally assigned, regardless of the degree of compliance with the intervention.

The results will be considered statistically significant when *p* < 0.05. The analyses will be performed using STATA16.

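### The measures credited with blinding allocation in data handling and analysis are pseudonymisation: they conceal who a participant is, not which arm the participant is in

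*Protocol article*

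**What the plan says.** Under Recruitment and allocation, in the paragraph after Figure 1, the article makes two separate statements about blinding. The first concerns outcome assessment: "the investigators involved in measurements will be blinded to the group to which the participants belong". The second concerns the analysis: "each participant will receive an identification number to blind his/her allocation during the analysis of data". The only separation described in support of the second is this: "The identification number and the personal data of the participants will be stored in different data bases". The two databases may be linked when abnormal values need checking.

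Analyses of outcomes adds a claim about data handling: "Blinding on handling data will be assured by separating measurement values from general participant information". The same section specifies the model, in which "interventions will be treated as fixed effects (1 = IG and 0 = CG", and closes with an intention-to-treat rule under which participants are kept in their assigned group whatever their compliance.

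The section on nonadherence and prolongation of training sets a condition for entering the analyses: "To be considered in the analyses, participants must attend at least 70% of the sessions". The intervention description says that control participants carry on with their usual daily activity, so they have no sessions to attend.

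**The concern.** Blinding of allocation during analysis means that the person who cleans the data, settles the analysis set and runs the models cannot tell which records belong to which arm. Removing names does not achieve this. An analyst who sees a participant number beside a group value of 1 does not know the person but does know the arm.

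The article recognises that participants cannot be blinded, so blinding of assessment and of analysis is the main remaining protection against bias. A reader will give the trial credit for a blinded analysis. If the described procedure does not provide one, any judgement left open at the data stage may be made with the arms in view. Two such judgements can be found in the text: how queries about abnormal values are resolved, and whether the attendance condition or the intention-to-treat rule decides who is analysed. The efficacy and feasibility phase plans 24 participants per group, so decisions on individual records could matter. The Design section says the implementation phase will follow the same procedures, so the wording would carry over.

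**Working it through.** No arithmetic applies. The check sets each claimed property beside the mechanism given for it and asks what the mechanism conceals.

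1. **Blinding in the analysis.** Claimed property: allocation is blinded. Mechanism: an identification number, stored apart from personal data. What it conceals: the link from number to person. The allocation list is not mentioned among the items kept apart, and nothing says that the arm is withheld from the analyst or relabelled.

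2. **Blinding in data handling.** Claimed property: blinding is assured. Mechanism: measurement values are kept apart from general participant information. What it conceals: whatever counts as general participant information, which the article does not define. If allocation is stored there, the two researchers who enter the data could be blind to group. That would not carry through to the analysis, because a comparison of arms requires the arm to be joined to the measurements at some point.

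3. **The arm variable.** Randomisation is 1:1 to two groups and the model contains a group term. The article gives that term as 1 for intervention and 0 for control. If the analysis file carries this code, the arm of every record in it is visible.

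4. **Session data.** The 70% condition can be applied only with attendance records, and those can arise only in the intervention group. Suppose the arm were relabelled A and B: once attendance is merged into the file, the label that has attendance records is the intervention group. Neutral codes alone would therefore not be enough while adherence data sit in the same file.

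5. **Which steps are exposed.** Winsorizing is not among them: it is fixed at the 1st and 99th percentiles and does not depend on arm. The model and its adjustment for baseline and age are also fixed. What remains open is the resolution of abnormal-value queries and the composition of the analysis set, where the 70% condition and the intention-to-treat rule pull in different directions.

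**The case against.** The strongest reply is that the 1/0 coding is only a model specification. Every two-arm model needs a group variable, and stating its coding tells the reader which way the coefficient points. It does not say what labels the analyst's file carries or when they are decoded. Separate storage is compatible with withholding the allocation list. Who holds a key and when it is opened are details that a condensed article often leaves to the full protocol or analysis plan, neither of which is shown.

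This stands against a stronger reading that a reader might infer: that blinding of the analysis does not exist, or that all 48 planned allocations (2 × 24) can be read. Both require the analysis file to carry the open code, which the article does not say. The reply does not rescue the published mechanism. The article names what achieves the blinding, and what it names conceals identity. A further measure in an unseen document would supplement that statement without making it correct.

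Three other inferences also fail:

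- **Outcome assessors.** The intervention description says of the platform data that "Research team will be able to check this information during the development of the session or at any time of the clinical trial duration". One might conclude that assessors are unblinded through these logs. Nothing says that assessors have access, or that the logs are indexed by study number, and the article states expressly that those who measure are blinded.
- **Choice among the primary endpoints.** This is a multiplicity and reporting matter. The choice could still be made after a key is opened, so masking would not cure it.
- **Abnormal values.** The text places the linking of databases at the measurement stage and describes a link to personal data, not to allocation. It is a point where masking is useful, not evidence that data are altered with the arm known.

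**Conclusion.** The point holds in a limited form. The identification number and the separation of files are pseudonymisation and do not by themselves blind allocation in data handling or analysis. The article attributes to them a property they do not have. Its open arm code, if carried into the analysis file, and the session data behind the 70% condition would each reveal the group.

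The conclusion rests on the published text alone and on one reading: that general participant information and personal data mean identifying details, not the allocation list. If allocation is kept with that information, data entry could be blind to group, but the analysis claim would still lack a mechanism. The size of any bias cannot be derived from the documents, and none is asserted. What is affected is the credibility of the blinding claim and the protection of the few data decisions still open. The statement that assessors are blinded is untouched.

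**What to change.** Amend the blinding paragraph under Recruitment and allocation and the opening of Analyses of outcomes to state four things:

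- The arm is supplied to the analyst under neutral codes, A and B.
- An existing team member who does not run the models holds the key.
- The key is opened only after data queries, analysis-set decisions and the primary model code are final.
- Adherence data stay out of the primary analysis file until then. The decision between the attendance condition and the intention-to-treat rule therefore has to be taken as a rule, before anyone handling that file sees attendance.

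The 1/0 coding can remain as the description of how the decoded coefficient is read. If the team does not want to adopt this procedure, the claim of blinded handling and analysis should be removed and only the blinding of assessors kept.

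The cost is small: some administration of the key and a delay before adherence data can be used. Measurements, sample size and the statistical model do not change.

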### Participants: inclusion and exclusion criteria

Participants will be invited to participate when meeting the following inclusion and exclusion criteria.

Inclusion criteria. Individuals: (1) aged 60–80 years of both genders; (2) retired regardless of the reason for retirement; (3) not meeting frailty criteria according to Fried criteria; (4) are without disabilities for activities of daily living; (5) live independently; (6) without cognitive impairment as determined by the Mini-Mental test greater than 24 (considering the degree of schooling of the participants); and (7) able to walk at least 20 meters with or without walking aids.

Exclusion criteria. Individuals will be excluded when they have any of the following: (1) mobility problems; (2) serious health problems (e.g., recent myocardial infarction, uncontrolled diabetes, or uncontrolled hypertension); (3) orthopedic or neurological disease that prevents training; (4) Alzheimer’s disease or dementia; (5) progressive or terminal illness; (6) acute or chronic illness; (7) history of heart attack; (8) history of vertigo or recent head injury; (9) health problems that may affect the ability to perform physical exercise (e.g., acute and painful joint inflammation, impaired joint function, acute and painful joint inflammation, or deterioration in the ability to perform physical exercise); (10) intake of medications that act at the neuron level (e.g., psychotropic medications); (11) signs of incipient depression; or (12) pathology that impedes the use of the computer application through which the physical exercise program will be developed.

### MOVI-ageing intervention: description

The MOVI-ageing intervention will be developed as a randomized controlled trial with two arms in which participants will be randomly assigned to the IG, in which a home-based e-Health intervention of cognitively demanding exercise will be performed, or to the CG in which participants will continue their regular daily activity.

The e-Health intervention will be delivered using a platform including videos that will guide the participants in the realization of the movement during the cognitively demanding physical exercises. The participants will follow the videos remotely and off-line, and the users will have to imitate the movements of the trainer. Through the platform, it will be possible to evaluate the degree of compliance with the exercise program and the correct performance, as the system will accurately track and measure the participant’s limb movement through the camera and provide the research team with an objective measure of the patient’s movements and progress. Research team will be able to check this information during the development of the session or at any time of the clinical trial duration.

The recorded videos, designed by a team of experts including nurses, psychologists, physical activity graduates, and geriatricians, will include cognitively demanding exercises involving both basic cognitive functions (i.e., inhibition, working memory, and cognitive flexibility) and higher cognitive functions (i.e., spatial orientation, numerical calculation, and semantics). Each video will include a standardized physical exercise program structured as follows: 5 min warm-up (including animation and/or joint mobility activities), three blocks of 4 min at 65–75% of the maximum heart rate (including aerobic and muscle strength activities) without cognitive demand, three blocks of 4 min at moderate intensity including cognitively demanding activities, and 10 min of cool-down (including balance activities, breathing-relaxation exercises, and/or muscle stretching) (Figure 2).

